##### Work Package 3: Team Management - Workstream 3: Maintain Strong Team Coordination

We will use weekly meetings, 4-week sprints, and cross-team synchronization meetings held every 2 weeks to align development and clinical goals. Centralized tools, shared repositories, and cross-team workshops will enable transparent communication and knowledge sharing for risk management. Progress tracking through key performance indicators and Agile feedback loops will ensure seamless integration, address stakeholder feedback, and align priorities for timely XR platform delivery.

### Participants: Number and Diversity

#### Patients With FMD

We plan to recruit up to 50 patients with FMD to account for variability in symptoms such as functional weakness and dystonia, enabling subgroup analyses. This sample size is based on statistical power analysis using SUS scores from pilot testing across 3 XR tasks (hypnotic relaxation, position feedback, and force feedback) [35]. An effect size (Cohen *d*) of 0.81 was calculated, indicating a large difference between usability scores for position feedback and force feedback tasks. With a significance level of .05 and 80% power, approximately 15 participants per group are needed for usability testing. Recruiting 50 patients ensures that the study is adequately powered to detect meaningful differences and supports robust platform refinement and clinical translation.

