**Methods:**

We propose to use an experience-based co-design framework to engage patients with FND, caregivers, and health care professionals in collaboratively designing the XR platform. Stakeholders can share their experiences through narrative interviews and co-design workshops, which can identify emotional touchpoints and prioritized patient-centered needs. Insights will be synthesized through qualitative analysis and used to guide the development of system requirements via quality function deployment, ensuring that the platform aligns with user needs. XR training tasks—virtual reality relaxation, XR position feedback, and XR force feedback—will be integrated as needed into a unified therapeutic game experience through 4-week Agile sprints. Usability will be assessed using the System Usability Scale and qualitative feedback, with themes analyzed in NVivo to identify key areas for subsequent improvement.

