The predesign study evaluated an XR-based biofeedback platform for upper limb rehabilitation in individuals with FND, developed through co-design with patients and clinicians. Among the 3 tested XR tasks, high usability scores (>85) were recorded for XR position feedback task, indicating excellent user satisfaction. By contrast, the VR relaxation task produced mixed reactions due to motion discomfort, and the XR force feedback task showed varied results depending on individual motor impairments, such as functional dystonia, emphasizing the need for personalized approaches. Qualitative feedback highlighted the importance of comfort, immersive content, personalization, and accessibility. Therefore, predesign study findings emphasized the potential of XR in FND rehabilitation but highlighted the need for personalized approaches to meet diverse patient needs in FND. The predesign study further demonstrated the promise of XR technology for functional motor disorder rehabilitation by embedding biofeedback training into a patient-centered game design framework. EBCD and QFD emerged as valuable methods for coproduction and to systematically address usability barriers. To deepen personalization, this study will incorporate portable brain imaging to assess dFC in key regions during XR intervention, enabling individually responsive dosing. Moreover, the themes for improvement identified from the predesign study included customization, comfort, accessibility, and technological quality.

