The usability testing revealed higher satisfaction with VR relaxation and XR position feedback tasks, aligning with the Delphi findings that underscored the importance of comfort and accessibility [35]. However, the variability in XR force feedback usability, particularly among participants with conditions such as functional dystonia, emphasizes the need for personalized approaches. These results support the Delphi survey recommendation for task-specific customizations and accessibility enhancements to ensure broader usability across diverse patient needs. The predesign study also underscored the importance of coproduction in designing rehabilitation technologies, as demonstrated by the mixed methods approach and Delphi framework. Engaging patients with FND and clinicians in the design process ensures that the technology addresses real-world challenges, such as motion sickness and sensory overload, highlighted in both the predesign and Delphi studies.

This study builds on prior predesign work in FND rehabilitation [35] and integrates key pathophysiological insights specific to functional limb weakness, namely deficits in sensory attenuation, motor intention encoding, and agency disruption, to refine the XR platform for this targeted clinical application. By aligning the XR interventions with these mechanistic targets, such as prediction error recalibration and intention-action coupling, the platform aims to deliver therapeutically relevant biofeedback experiences. Patient-specific adjustments, including calibration for individual motor impairments and optimization of sensory inputs, are incorporated to enhance comfort, usability, and therapeutic responsiveness. Using a structured EBCD process, our approach supports meaningful engagement with patients and caregivers, ensuring that the technology remains responsive to their evolving needs. The platform’s modular design, guided by insights from both iterative usability testing and Delphi surveys, positions it for broader integration into a stepped care FND model, facilitating sustained improvements in functional outcomes and patient experience from clinic to home.

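### The claim that 50 patients are adequate is powered on a pilot contrast between two tasks, which is not a stated aim of this study, and the figure of 15 per group holds only for a paired comparison

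*Protocol article*

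**What the plan says.** The sample-size paragraph (Participants: Number and Diversity, Patients With FMD) opens: "We plan to recruit up to 50 patients with FMD to account for variability in symptoms such as functional weakness and dystonia, enabling subgroup analyses". It continues: "This sample size is based on statistical power analysis using SUS scores from pilot testing across 3 XR tasks". The only effect size given is Cohen d = 0.81, "indicating a large difference between usability scores for position feedback and force feedback tasks". With a significance level of .05 and 80% power, the paragraph derives approximately 15 participants per group. It then states: "Recruiting 50 patients ensures that the study is adequately powered to detect meaningful differences".

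Elsewhere the article describes a different question:

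- The Objective in the Abstract is to coproduce one XR platform and evaluate its usability, with a focus on functional limb weakness.
- The Methods in the Abstract say that the relaxation, position and force tasks "will be integrated as needed into a unified therapeutic game experience through 4-week Agile sprints".
- Workstream 2a brings 50 patients to three alternate-day clinic visits to evaluate SUS scores and clinical validity. It names no arms or comparison groups.

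On the population, Textbox 1 excludes other FMD subtypes and names dystonia as an example. Of the pilot, the Predesign Study section reports that "the XR force feedback task showed varied results depending on individual motor impairments, such as functional dystonia". The Discussion (Summary) likewise places the variability of force-feedback usability particularly among participants with conditions such as functional dystonia.

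**The concern.** A power statement is about one comparison. Here it is about a within-pilot difference between two tasks, while the study sets out to learn how usable the integrated platform is in one cohort of patients. High power for the first says nothing about how precisely the second will be answered. Yet the paragraph draws a general conclusion, that the study is adequately powered, which ethics reviewers and readers will take to cover the usability evaluation and the subgroup analyses.

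Two features of the paragraph add to the problem. The words per group do not fit a design with no groups, and they change what the figure of 15 means. The effect size also comes from a pilot that included functional dystonia, and the article contradicts itself on whether such patients will be among the 50.

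**Working it through.** **Inputs from the article.** d = 0.81, significance level .05, power 80%, about 15 per group, and up to 50 patients (all from Patients With FMD). The article does not say whether the test is one- or two-sided, or paired or independent. I take it as two-sided and try both designs.

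**Step 1: reproduce the figure of 15.**

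- Paired t-test, with d read as the mean within-patient difference divided by the SD of the differences. The normal approximation is n = ((1.960 + 0.842)/0.81)² = 11.96, so 12. The t-test solution is n = 14.004, which rounds up to 15. Power at n = 15 is 0.83.
- Independent groups. The normal approximation is n = 2 × ((1.960 + 0.842)/0.81)² = 23.9, so 24 per group. The t-test solution is 24.92, so 25 per group. Power at 15 per group is 0.57.
- One-sided versions give 11 (paired t) and 20 per group (independent t). Neither is 15.

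The stated figure is therefore correct for about 15 patients in total who each rate both tasks. It is not correct for 15 patients in each of two groups.

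**Step 2: does 50 follow from it?** For the paired contrast at d = 0.81, 50 patients give power of about 0.9999. So 50 does not come from this calculation. The paragraph attributes it to symptom variability and subgroup analyses.

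**Step 3: the subgroup analyses.** The article gives no subgroup effect or split. As an illustration only, I apply d = 0.81 to a difference between two independent subgroups of the 50:

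| Split | Power |
|---|---|
| 25/25 | 0.80 |
| 35/15 | 0.73 |
| 40/10 | 0.61 |
| 45/5 | 0.39 |

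**Step 4: what 50 patients offer for platform usability.** The 95% CI half-width for a mean SUS is t(0.975, n−1) × SD/√n. The article gives no SUS SD, so I assume a range. The 45 evaluable patients are also an assumption.

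| Assumed SD | n = 50 | n = 45 |
|---|---|---|
| 12.5 | 3.6 | 3.8 |
| 15 | 4.3 | 4.5 |
| 20 | 5.7 | 6.0 |
| 25 | 7.1 | 7.5 |

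For example, t(0.975, 49) = 2.010 and √50 = 7.071, so an SD of 15 gives 2.010 × 15/7.071 = 4.26.

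**Step 5: does 0.81 carry over?** Textbox 1 excludes dystonia. The sample-size paragraph expects it among the 50. The pilot included it. The article gives neither the share of pilot participants with dystonia nor any mean or SD by subtype, so the effect of their exclusion on d cannot be calculated.

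**The case against.** The strongest reply is that the sample is comfortable. On the paired reading, 50 patients give 80% power even at half the pilot effect (d = 0.405). The figure of 31% at that effect belongs to 15 patients, which is not the planned number. This stands. A reader might infer that the study is too small, and nothing in the document shows that. The half-widths above rest on assumed SDs and do not make 50 inadequate either.

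A second reply is that the two tasks may still be compared. The Abstract says they are integrated only as needed, the small-group work lists force and position games as separate constructs, and an analysis plan may exist. This stands too: it would go too far to say that the contrast will never be tested. But the article does not state it as an aim and still rests a general adequacy claim on it.

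A reader might also infer that d must shrink once dystonia is excluded. The article ties dystonia to variability in force-feedback usability, not to a larger mean difference. If exclusion lowers the SD, d can rise. With assumed values of mean difference 12 and SD 12 in limb weakness, mixed with 30% dystonia at mean 30 and SD 30, the pooled mean is 0.7 × 12 + 0.3 × 30 = 17.4. The pooled variance is 0.7 × (144 + 5.4²) + 0.3 × (900 + 12.6²) = 438.8, so d = 17.4/20.9 = 0.83. Without dystonia, d = 12/12 = 1.00. Other assumptions lower it.

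Finally, the relaxation task is described as having "the VR relaxation task produced mixed reactions due to motion discomfort" in one section, while the Discussion says: "The usability testing revealed higher satisfaction with VR relaxation and XR position feedback tasks". This does not undermine the power calculation, because relaxation does not enter d = 0.81.

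**Conclusion.** The concern holds for the justification, not for the number of patients. The adequacy claim rests on one pilot contrast that the article does not state as an aim, and it is not shown for platform usability, clinical validity or subgroup analyses. The figure of 15 is right only as a paired total (power 83%). As worded, per group, it would correspond to 57% power, and 25 per group would be needed for 80%. Subgroup comparisons at the same d would have 80% power at best (25/25) and 61% at 40/10.

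The eligibility statements conflict, so d = 0.81 cannot be assumed to apply to the 50, whether too high or too low.

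The results assume a two-sided test and, for the reproduction of 15, a paired design. The SUS precision figures depend on the assumed SDs.

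**What to change.** Keep the 50 patients and change the text:

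1. Replace the adequacy claim with a precision statement for mean SUS of the integrated platform at a named visit, for both 50 and a stated number of evaluable patients. For example, an SD of 15 would give a half-width of 4.3 points with 50 patients and 4.5 with 45.
2. Reconcile Textbox 1 with the sample-size paragraph on dystonia, then take the SD from pilot participants who match the reconciled criteria.
3. Describe the d = 0.81 calculation as a paired one needing about 15 patients in total, and drop the words per group. Keep position versus force only as a secondary paired comparison, and only if the tasks are still rated separately.
4. Describe the subgroup analyses as exploratory.

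The cost is wording, a decision on the conflicting eligibility statements, and a look back at the pilot data for the SD. The downside is that the stated justification becomes less favourable.

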##### Work Package 2: Advancing Usability, Validity, and Strategic Delivery

###### Workstream 2a: Clinical Usability and Ecological Validity Testing

Usability studies will be conducted with 50 patients with FMD for 3 alternate-day clinic visits, evaluating SUS scores and the platform’s clinical validity in a safe, controlled setting. Deployment-time guardrails will be responsible for executing real-time performance monitoring and error detection, as well as initiating fallback procedures during the XR platform operation under controlled clinical conditions.

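### The stated 15 participants per group does not follow from d = 0.81 at 80% power: independent groups need 25 each, and 15 is right only as a paired total

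*Protocol article*

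**What the plan says.** Under Patients With FMD, the article says "We plan to recruit up to 50 patients with FMD" and bases this on a "statistical power analysis using SUS scores from pilot testing across 3 XR tasks". The effect size is a Cohen d "of 0.81 was calculated, indicating a large difference between usability scores for position feedback and force feedback tasks". The calculation then reads "With a significance level of .05 and 80% power", followed by the result that "approximately 15 participants per group are needed for usability testing". The paragraph names neither the test, nor its sidedness, nor the groups. It also gives a second reason for 50: to cover variability in symptoms and allow subgroup analyses.

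The patient usability study itself is described under Workstream 2a: "Usability studies will be conducted with 50 patients with FMD for 3 alternate-day clinic visits". That section mentions no parallel groups and no allocation of patients to tasks.

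**The concern.** A sample size expressed per group normally means independent groups. With d = 0.81, 15 per group is well short of what 80% power requires in that design. The effect size, however, is a contrast between two tasks, and Workstream 2a describes one cohort, which points to a within-patient comparison. In that case there are no groups, and the unit is wrong.

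This is the only power statement in the article. It is offered as the basis for the sample size, and the same paragraph promises subgroup analyses. A reader who accepts 15 per group as sufficient could regard subgroups of that size as adequate for comparisons between them.

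**Working it through.** **Inputs.** d = 0.81, alpha = .05 and power = 80%, all from Patients With FMD. Sidedness is not stated; two-sided is assumed, and one-sided is also shown. Power comes from the noncentral t distribution.

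**Step 1: reproduce the stated 15.** For a paired (one-sample) t test with n patients, the noncentrality is d_z × √n on n − 1 degrees of freedom. Take 0.81 as d_z, two-sided.
- Solving for 80% power gives n = 14.004, which rounds up to 15.
- At n = 15 the noncentrality is 0.81 × √15 = 3.137, the critical t on 14 df is 2.145, and power is 83.1%.

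So 15 is reproduced as a total number of patients.

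**Step 2: take the unit literally.** For two independent groups of n each, the noncentrality is d × √(n/2) on 2n − 2 degrees of freedom.
- Two-sided: n = 24.92, so 25 per group. At 25 the noncentrality is 0.81 × √12.5 = 2.864, the critical t on 48 df is 2.011, and power is 80.1%.
- Two-sided at 15 per group: the noncentrality is 0.81 × √7.5 = 2.218, the critical t on 28 df is 2.048, and power is 57.2%.
- One-sided: n = 19.56, so 20 per group; 15 per group gives 69.8%.
- Normal approximation: 24 per group two-sided, 19 one-sided.

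None of these independent-group calculations comes near 15.

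**Step 3: how far the paired reading depends on the standardiser.** If 0.81 was divided by the between-patient SD, then d_z = 0.81 / √(2(1 − r)), where r is the correlation of the two task scores within a patient. The documents give no r, so the range is an assumption.

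| r | d_z | Patients for 80% power | Power with 50 |
|---|---|---|---|
| 0 | 0.573 | 26 | 97.8% |
| 0.25 | 0.661 | 20 | 99.6% |
| 0.5 | 0.810 | 15 | >99.9% |
| 0.7 | 1.046 | 10 | >99.9% |

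At r = 0.5 the factor √(2(1 − r)) equals 1, so the two definitions coincide.

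**Step 4: what 50 patients deliver.** Split 25/25, power for d = 0.81 is 80.1%. Paired, power is at least 97.8% over the range of r above, and the smallest d_z detectable with 80% power is 0.404.

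**The case against.** The strongest defence is that 15 is not a miscalculation. It is what a two-sided paired t test gives, the contrast is between tasks, and the study is one cohort, so the fault is a loose label. No arm of 15 is described anywhere. The plan recruits up to 50, with symptom variability and subgroups as a further reason to exceed the minimum. An article may also leave the standardiser and the within-patient correlation to a fuller document.

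Most of this stands. The paired reading is the likelier one, and the unstated standardiser is not itself an error; the table in the working only shows what the figure would depend on. But the defence does not rescue the sentence: a paired calculation has no groups, so the printed unit is wrong on that reading, and the printed number is wrong on the other. The words might instead refer to symptom subgroups, or to patients and healthy participants, of whom about 15 are also planned. The text does not say so, and a between-group contrast of 15 against 15 at d = 0.81 would again have 57% power.

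A reader might infer that the usability study is underpowered, for instance by supposing that the 50 patients are divided among the three tasks. The documents do not support this: no section allocates patients to a single task, and 50 patients reach 80% power as two groups of 25 or as a paired sample.

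**Conclusion.** The statement is wrong as printed. With d = 0.81, alpha .05 and 80% power, independent groups need 25 each (two-sided), and 15 each gives 57%. The figure 15 holds only as a total for a two-sided paired comparison with d_z = 0.81. A paired calculation with the wrong unit is the probable explanation, but this is an inference, because the article does not state that the same patients perform both tasks.

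The main comparison is not shown to lack power. That conclusion assumes that all 50 patients are recruited, whereas the plan says up to 50. Under a two-group reading 50 leaves no margin, since 20 per group would give 70.4%; under a paired reading the margin is wide. Severity is minor to moderate: the justification needs correcting, but the planned number can stand.

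**What to change.** Rewrite the calculation in Patients With FMD according to the intended design.

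- If the comparison is within patients, say that each patient performs both tasks and replace the per-group figure with 15 patients in total (paired t test, two-sided, d_z = 0.81). Confirm that 0.81 was standardised by the SD of the within-patient differences; if it was not, give the assumed correlation and the resulting number.
- If independent groups are meant, define them and write 25 per group.

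In either case, add what 50 patients deliver: 80.1% power for d = 0.81 as 25 against 25, or a detectable paired d_z of about 0.40 at 80% power. Do not present 15 as an adequate size for comparisons between subgroups.

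The cost is a few sentences in one paragraph. No extra patients are needed.

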#### Healthy Participants

Approximately 15 healthy participants will be included in the pilot studies in work package 1 to validate usability, construct validity, and core platform functions through a test-retest study over 6 repeats. Participants will be drawn from diverse backgrounds, focusing on inclusivity across socioeconomic groups, ages, and underrepresented populations. Given the higher prevalence of FMD in female individuals, recruitment efforts will emphasize female participation.

### Recruitment and Engagement

Collaboration with FND charities (eg, FND North and FND Action) and patient advocates will support recruitment, ensuring diverse participation through purposive sampling. EBCD processes will be used to coproduce the XR platform with participants, aligning the development with stakeholder needs.

### Procedures

Initial studies will take place in controlled laboratory settings at the Lancashire Clinical Research Facility to prioritize safety. Studies involving patients with FMD will be conducted under clinical supervision.

### Areas of Substantial or Moderate Impact

Minimal physical risks are anticipated with XR use. Co-design efforts will address known discomforts such as eyestrain, and iterative feedback will ensure participant safety and well-being during XR tasks. Recognizing the vulnerability of patients with FMD, therapeutic environments within the XR platform will be carefully co-designed to prevent distress, guided by feedback from the EBCD process. Transparent consent processes, stringent deidentification protocols, and active stakeholder collaboration will mitigate ethical risks associated with the research.

## Results

**Predesign Study**

The predesign study, supported by EPSRC Network+ funding, investigated the usability of an XR neurotechnology platform for FND rehabilitation, focusing on biofeedback training for functional limb weakness [35] (Multimedia Appendix 1). In the first round of a Delphi survey (a structured expert consensus method involving multiple rounds of questionnaires to refine opinions or priorities) involving 20 participants with lived experience of FND, there was strong consensus on the potential of VR with haptics for biofeedback-based motor rehabilitation. Participants highlighted the immersive experience, real-time feedback, and customizable environments as key advantages for improving motor control in functional limb weakness. However, several barriers to adoption were identified including high equipment costs, limited accessibility through public health care systems, concerns around usability (eg, motion sickness, technical learning curve), and sensory overstimulation. These findings informed subsequent predesign study of a home-based rehabilitation system integrating operant conditioning within mixed-reality environments. Limited accessibility through public health care systems prompted the need for the integration of patient-centered cost-effectiveness analysis in coproduction that accounts for disease severity, disability, and individual preferences thereby addressing limitations in traditional QALY models.

The predesign study evaluated an XR-based biofeedback platform for upper limb rehabilitation in individuals with FND, developed through co-design with patients and clinicians. Among the 3 tested XR tasks, high usability scores (>85) were recorded for XR position feedback task, indicating excellent user satisfaction. By contrast, the VR relaxation task produced mixed reactions due to motion discomfort, and the XR force feedback task showed varied results depending on individual motor impairments, such as functional dystonia, emphasizing the need for personalized approaches. Qualitative feedback highlighted the importance of comfort, immersive content, personalization, and accessibility. Therefore, predesign study findings emphasized the potential of XR in FND rehabilitation but highlighted the need for personalized approaches to meet diverse patient needs in FND. The predesign study further demonstrated the promise of XR technology for functional motor disorder rehabilitation by embedding biofeedback training into a patient-centered game design framework. EBCD and QFD emerged as valuable methods for coproduction and to systematically address usability barriers. To deepen personalization, this study will incorporate portable brain imaging to assess dFC in key regions during XR intervention, enabling individually responsive dosing. Moreover, the themes for improvement identified from the predesign study included customization, comfort, accessibility, and technological quality.

